### Eligibility and non‐eligibility

2.2

This study focuses on HFrEF patients who meet the criteria for receiving ICD for primary and secondary prevention of SCD and those who meet the criteria for WCD for primary prevention. Participants must be 20 years of age or older at the time of obtaining consent and provide written consent based on their own free will after receiving sufficient explanation regarding participation in this study. Patients eligible for this study will be basically fulfilled with the criteria of class I or IIa for ICD including sub‐cutaneous ICD (*S*‐*ICD*), and WCD as outlined in the JCS guidelines^1^: (1) patients with coronary artery disease (CAD) (≥40 days after myocardial infarction (MI) and at least 90 days after revascularization) or non‐ischemic cardiomyopathy who have NYHA class II or greater symptoms and an LVEF ≤35% despite optimal medical therapy, irrespective of whether they've experienced NSVT (criteria for primary prevention of SCD), (2) CAD or non‐ischemic cardiomyopathy who have NYHA class II or greater symptoms and an LVEF ≤35% accompanied by ventricular fibrillation (VF) or out‐of‐*hospital* cardiac *arrest* requiring electrical shock, sustained VT or unknown syncope, not due to reversible causes (criteria for secondary prevention of SCD), and (3) patients with LVEF ≤35% and HF symptoms of NYHA class II or III, and within 40 days after the onset of acute MI, and are within 90 days after coronary artery bypass or percutaneous coronary intervention, or within 90 days after the acute onset of HF due to a non‐ischemic etiology (WCD criteria). Therefore, this study will also include the patients who have opted not to receive ICD or WCD based on the patients' preference, including those without any cardiac device or those with CRT‐P. The following patients are excluded from this study: (1) those with a life expectancy of less than 12 months, (2) patients with frequent recurrent VT or VF that cannot be controlled with antiarrhythmic drugs or catheter ablation, (3) severe HF patients classified as NYHA class IV, (4) individuals unable to provide consent for the study, and (5) others judged unsuitable as study subjects by the principal researcher.

In short, the target cases for this study are those aged 20 or older with LVEF ≤35% and NYHA class II or higher HF symptoms despite adequate medical therapy, who do not fall under the exclusion criteria mentioned above.

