Date of informed consent Age, gender, height, weight Smoking habits: Current/Former/Never Alcohol consumption: Daily / 2–3 times a week/Never Underlying heart disease (Ischemic cardiomyopathy/non‐ischemic cardiomyopathy [Dilated cardiomyopathy/hypertrophic cardiomyopathy/hypertensive heart disease/others]) NYHA functional classification (I/II/III/IV) Medical history (Diabetes, hypertension, dyslipidemia, ischemic heart disease [History of myocardial infarction/Angina], history of heart failure, chronic obstructive pulmonary disease, history of stroke, peripheral arterial disease) Clinical Frailty Scale: 1–9 Medication History ① Beta‐Blockers: Yes/No ② ACEi/ARB (angiotensin‐converting enzyme inhibitor / angiotensin receptor blocker): Yes/No ③ Mineralocorticoid Receptor Antagonists: Yes/No ④ ARNi (Angiotensin Receptor‐Neprilysin Inhibitor): Yes/No ⑤ SGLT2i (Sodium‐Glucose Cotransporter 2 Inhibitors): Yes/No ⑥ Ivabradine: Yes/No ⑦ Pimobendan: Yes/No ⑧ Digoxin Preparations: Yes/No ⑨ Antiarrhythmics: Sodium Channel Blockers (Procainamide/Disopyramide/Flecainide/Cibenzoline/ Pirmenol/Aprindine/Propafenone), Potassium Channel Blockers (Amiodarone/Sotalol/Bepridil) ⑩ Anticoagulants: Warfarin/Direct Oral Anticoagulants (DOACs) ⑪ Antiplatelet Agents: Yes/No ⑫ Lipid‐Lowering Medications: Yes/No ⑬ Diabetes Medications (excluding SGLT2i): Yes/No History of revascularization (percutaneous coronary intervention, coronary artery bypass grafting) Presence of atrial fibrillation/flutter (paroxysmal/persistent/permanent) Presence of NSVT (≥5 beats) History of ablation therapy for NSVT/VT History of cancer (gastrointestinal/lung/other) Dialysis (yes/no) Echocardiogram (LVEDV [mL], LVESV [mL], LVDd [mm], LVDs [mm], LAD [mm], LVEF [%], presence of moderate or severe valvular disease [MR, TR, AR, AS]) Electrocardiogram (heart rate, rhythm, QRS duration [ms], presence of ventricular pacing) Laboratory data (NTproBNP [pg/mL] or BNP [pg/mL], WBC [×10^9^/L], lymphocyte count [×10^9^/L], Hb [g/dL], Plt [×10^9^/L], BUN [mg/dL], Cr [mg/dL], eGFR [mL/min/1.73 m^2^], UA [mg/dL], AST [U/L], ALT [U/L], rGTP [U/L], Tcho [mg/dL], Na [mmol/L], K [mmol/L], TP [g/dL], Alb [g/dL], CRP [mg/dL]) Confirmation of performance only Signal‐averaged electrocardiogram (present/absent) Holter monitoring (present/absent) Cardiac MRI (present/absent)
(2) At 12 Months (±3 Months) (WCD indication group: at 3 Months corresponding to the time of WCD removal phase and 12 months after removal phase)

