Device introduction For a case who are decided to receive no device implantation: Reasons for no introduction: (1) Patient does not want risk associated with implantation. (2) Patient does not believe in benefit of ICD/CRT‐D/WCD. (3) Patient unable to pay for device. (4) Other reasons. For a case of introduction: Date of device implantation, indication for device implantation (primary prevention / secondary prevention), type of device and product name (WCD/ICD/CRT‐P/CRT‐D/other), (new implantation/upgrading) For a WCD case, the date of removal Invasive treatments during follow‐up Date of invasive treatment, type of invasive treatment (implantable cardiac device/implantable loop recorder/catheter ablation/revascularization/device reoperation) Clinical event investigation Event Date ① Presence of VT (five or more consecutive beats), VF, and/or shock events (including inappropriate shocks) ② Presence of death (cardiovascular death, other causes of death: specify details) ③ Hospitalization due to heart failure ④ Other cardiovascular events requiring hospitalization ⑤ Stroke/TIA and systemic embolism ⑥ Myocardial infarction, unstable angina ⑦ Major bleeding (ISTH criteria) ⑧ Clinically significant bleeding

Abbreviations: CRT‐D, cardiac resynchronization therapy defibrillator; CRT‐P, cardiac resynchronization therapy pacemaker; ICD, implantable cardioverter defibrillator; ISTH, International Society on Thrombosis and Haemostasis; TIA, transient ischemic attack; VT, ventricular tachycardia; VF, ventricular fibrillation; WCD, wearable cardioverter defibrillator.

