### Primary and secondary endpoints

2.4

The primary endpoint is the rate of cardiac implantable electronic device implementation. The secondary endpoints are shown in Table 4. Other significant factors besides the primary endpoint include the incidence of VT/VF, the presence of sudden death, all‐cause mortality, and HF hospitalization, as well as other variables. We will gather standard clinical background information, each patient's Clinical Frailty Scale score, laboratory test results (including measures of nutritional status), and serial changes, which will also serve as secondary endpoints.

**TABLE 4 joa313028-tbl-0004:** Primary and secondary endpoints.

Primary endpoint	
Rate of cardiac electronic device implantation (ICD, CRT‐D, WCD, CRT‐P, or None)	
Secondary endpoints	
Occurrence of any of the following	
1. VT/VF and Sudden death^a^	
2. Death from any cause	
3. Cardiovascular events (stroke/TIA or systemic embolism, myocardial infarction/unstable angina, cardiovascular death [including sudden cardiac death], hospitalization for heart failure, or other cardiovascular event requiring hospitalization)	
4. Stroke/TIA or systemic embolism	5. Myocardial infarction/unstable angina
6. Heart failure requiring hospitalization or other cardiovascular event requiring hospitalization	
7. Major bleeding (ISTH criteria^b^)	8. Clinically significant bleeding
9. Major bleeding or clinically significant bleeding	10. Cardiovascular death
11. Other causes of death	12. Device‐related complications
13. Invasive cardiac interventions (surgery, catheter‐based treatments, pacemaker implantation, etc.)	
14. If patients refused implantation, reasons for ICD/CRT‐D/WCD implantation refusal (1. Patient does not want risk associated with implantation, 2. Patient does not believe in benefit of ICD/CRT‐D/WCD, 3 Patient unable to pay for device, or 4 Other reasons)	
Change in the following from the time of enrollment to 1 year (WCD cases: at the time of WCD removal and 12 months after removal):	
1. NYHA (New York Heart Association) functional classification, Clinical Frailty Scale	
2. Echocardiographic measures	
3. Hemoglobin, hematocrit, creatinine, NT‐proBNP or BNP	
4. Nutritional status markers (serum albumin concentration, white blood cell count [peripheral blood lymphocyte count], total cholesterol, C‐reactive protein)	

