Clinical events, such as VT/VF and sudden death, and cardiovascular events, for each group will be reported as percentages of the total population and annual frequencies per person‐year. Additionally, we will utilize the Kaplan–Meier method to calculate the cumulative event rates of clinical events, particularly focusing on VT/VF and sudden death, in the ICD/CRT‐D group, the non‐ICD (no device/CRT‐P) group among patients eligible for primary prevention, and compared these two groups using the log‐rank test. We will conduct Cox proportional hazards analysis to estimate hazard ratios (HRs) and 95% confidence intervals (CIs) for factors related to clinical events. Since the cardiovascular event rate is expected to provide sufficient data for multivariate analysis, we will conduct multivariate analysis to calculate the HR and 95% CI of the non‐ICD (no device/CRT‐P) group relative to the ICD/CRT‐D group in primary prevention for cardiovascular events by adjusting for clinically relevant factors. Based on the HINODE study, the annual occurrence rate of appropriate therapy for VT/VF with heart devices was approximately 6%. The all‐cause mortality rate for the group that did not have an ICD implanted (non‐device and pacing cohorts) was in the range of 8% (over the entire observation period).^17^ In the MADIT‐RIT Trial, the rate of appropriate ICD operation was also above 6%.^24^ In the MADIT II Trial, the rate of sudden cardiac death was approximately 10% in the non‐ICD group and less than 4% in the implanted ICD group, respectively.^15^, ^25^ Considering the low incidence of VT/VF and sudden death in primary prevention (approximately 5%–10%), the limited number of events may render multivariate Cox proportional hazards analysis impractical. Therefore, the propensity score model will be developed using selected variables according to clinical relevance. We will again draw the Kaplan–Meier method along with HR and 95% CI for VT/VF and sudden death for the propensity matched non‐ICD patient group compared with the propensity matched ICD patient group in primary prevention. As such, the results of elected patients after propensity score matching, along with all cohorts, along will be presented in the main text. For other groups, like those eligible for secondary prevention ICD and WCD, we plan to conduct the most comprehensive adjustment analysis possible, considering that the adjustable variables may change with the increasing number of cases.

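### The ICD versus non-ICD hazard ratio for VT/VF and sudden death mixes probable unequal detection of a loosely defined VT component with treatment effect and confounding

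*Protocol article*

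**What the plan says.** Table 4 of the protocol article lists, as the first secondary endpoint, "VT/VF and Sudden death". Its footnote defines sudden death. VT is given no duration or therapy criterion, and shocks are not mentioned.

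Table 3 lists what sites record during follow-up. The arrhythmia item is "Presence of VT (five or more consecutive beats), VF, and/or shock events (including inappropriate shocks". Table 2 records at baseline "Presence of NSVT (≥5 beats", which is the same beat threshold. Section 2.2 admits primary-prevention patients "irrespective of whether they've experienced NSVT".

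Section 2.6 compares ICD/CRT-D with non-ICD (no device or CRT-P) patients in primary prevention by Kaplan–Meier curves and the log-rank test, with particular attention to this composite. After propensity matching it adds: "We will again draw the Kaplan–Meier method along with HR and 95% CI for VT/VF and sudden death". Matched and full-cohort results are both intended for the main text.

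The rates quoted in section 2.6 are for narrower events. One cited study is said to show that "the annual occurrence rate of appropriate therapy for VT/VF with heart devices was approximately 6" per cent. Another is cited for sudden cardiac death of about 10% without an ICD and under 4% with one. The text then reasons: "Considering the low incidence of VT/VF and sudden death in primary prevention (approximately 5%–10" per cent), and prefers a propensity score to multivariable Cox regression for that reason.

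On monitoring, section 2.3 and Tables 1 and 2 schedule ECGs at registration and at the follow-up visits. Holter monitoring is a present/absent item at registration. The limitations paragraph of the Discussion names confounding but not outcome detection.

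**The concern.** In this comparison, exposure and outcome measurement are linked. A defibrillator monitors rhythm continuously and stores what it sees. A patient without a device contributes a VT/VF event only if it causes symptoms, leads to care or happens to be recorded. Part of any difference in VT/VF between the groups would then be a difference in looking.

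The loose definition makes this worse. The only VT threshold in the article is five beats, which is also the baseline NSVT threshold, and short runs are the events most likely to be seen by a device and missed otherwise. If inappropriate shocks also count, one component can arise only in patients with a defibrillator.

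The error runs against the ICD group: more of its events are found, which pulls the non-ICD versus ICD hazard ratio down. Matching balances baseline covariates and leaves outcome detection as it was. At stake is a main-text result that could hide a real difference in sudden death, in a study whose second purpose is to compare outcomes with and without a device.

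**Working it through.** The plan states no hazard ratio or event number for this composite, so there is no figure to reproduce. The target of 651 is a feasibility number and does not depend on this endpoint. The check asks what hazard ratio the planned comparison would be expected to show.

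**Inputs from section 2.6**
- VT/VF: 6% (appropriate therapy, annual).
- Sudden death: 10% without an ICD and 4% with one (the text says under 4%).

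**Assumptions not in the documents**
- All three rates share one time horizon.
- Hazards are constant, and the components act independently.
- True VT/VF incidence is the same in both groups.
- A share s of VT/VF is detected without an ICD, and all of it with one. The documents give no value for s; 10%, 25% and 50% are shown.

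**Formulas**
- Hazard from a proportion: h = −ln(1 − p). So h(6%) = 0.0619, h(4%) = 0.0408 and h(10%) = 0.1054.
- ICD composite hazard = 0.0619 + 0.0408 = 0.1027.
- Non-ICD composite hazard = s × 0.0619 + h(sudden death without ICD).
- HR = non-ICD hazard / ICD hazard.

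**Sudden death alone, plan's rates:** 0.1054 / 0.0408 = 2.58.

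**Composite**

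| s | Sudden death 10% vs 4% | Sudden death 4% in both |
|---|---|---|
| 10% | (0.0062 + 0.1054) / 0.1027 = 1.09 | (0.0062 + 0.0408) / 0.1027 = 0.46 |
| 25% | (0.0155 + 0.1054) / 0.1027 = 1.18 | (0.0155 + 0.0408) / 0.1027 = 0.55 |
| 50% | (0.0309 + 0.1054) / 0.1027 = 1.33 | (0.0309 + 0.0408) / 0.1027 = 0.70 |
| 100% | (0.0619 + 0.1054) / 0.1027 = 1.63 | 1.00 |

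The last row matters for attribution. Adding a VT/VF component that does not differ between groups already takes 2.58 down to 1.63 with perfect detection. Unequal detection accounts for the further fall from 1.63 to between 1.09 and 1.33.

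**CRT-P in the non-ICD group.** Suppose 10% to 30% of that group have a CRT-P that detects as fully as an ICD, and s = 10% in the rest (both assumed). The effective s is 0.10 + 0.90 × 0.10 = 0.19, up to 0.30 + 0.70 × 0.10 = 0.37. With equal sudden death the HR becomes (0.19 × 0.0619 + 0.0408) / 0.1027 = 0.51, up to (0.37 × 0.0619 + 0.0408) / 0.1027 = 0.62, against 0.46 with no CRT-P. The bias shrinks but remains.

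**Inappropriate shocks, if they counted.** At an assumed 2% or 5% in the ICD group only, with detection otherwise equal and no true difference, the HR is 0.1027 / (0.1027 + 0.0202) = 0.84 or 0.1027 / (0.1027 + 0.0513) = 0.67.

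**The case against.** Several points on the other side are sound.

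- **Table 3 is a collection list, not the endpoint definition.** Table 4 names neither shocks nor five-beat runs, and the rates quoted in section 2.6 suggest that a narrower endpoint was intended. A reader might infer that every short device-logged run and every inappropriate shock is an endpoint event. The article does not say so. What stands is that it does not say the opposite either, and five beats is the only VT threshold it gives.
- **The article states no ascertainment method for either group.** A reader might infer that VT/VF is device-recorded in one group and only clinically noticed in the other. That goes too far: the non-ICD group includes CRT-P patients, and loop recorders appear among the recorded procedures. Unequal detection is inferred from how the devices work and from a follow-up schedule that provides only ECGs. The inference is strong, but the monitored patients are only part of the non-ICD group.
- **Sudden death needs no device to be seen.** Untreated VF without an ICD may surface as sudden death and so still be counted, which is a reason to pair the two components. The hazard ratio is therefore not a pure measure of detection.
- **Part of the remedy is already there.** All-cause death is a secondary endpoint, the narrative in section 2.4 names sudden death separately, and the multivariable comparison in section 2.6 uses cardiovascular events, whose Table 4 definition does not name VT/VF. The composite nevertheless remains the focus of the log-rank and matched analyses.
- **The endpoint is secondary, and the Discussion disclaims causal conclusions.** This limits the severity. That disclaimer concerns confounding, however, and would not alert a reader to a detection difference.

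**Conclusion.** The concern holds as a point that should be fixed before analysis. The hazard ratio for VT/VF and sudden death cannot be read as a comparison of risk, because it combines detection, treatment effect and confounding, and matching addresses only measured confounding.

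With the plan's own rates, a sudden-death hazard ratio of 2.58 would appear as about 1.09 to 1.33 in the composite at detection shares of 10% to 50%. With no true difference, the composite would show about 0.46 to 0.70 instead of 1.00. Both ranges rest on the assumed detection shares, a common time horizon, equal true VT/VF incidence and independent components.

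A reader might go further and conclude that the planned analysis will reverse a real benefit. The plan's figures do not show that: on them the composite is attenuated and stays above 1. Reversal appears only if short runs count and are common. For example, an assumed VT incidence of 20% (hazard 0.2231) with s = 10% gives (0.0223 + 0.1054) / (0.2231 + 0.0408) = 0.48. The documents give neither that rate nor that counting rule.

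The primary endpoint, the device implantation rate, is not affected. The mismatch between the 5–10% incidence and the wider collection item does not touch the sample size either, since 651 was set by feasibility.

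**What to change.** 1. In section 2.6, base the ICD/CRT-D versus non-ICD Kaplan–Meier, log-rank and propensity-matched comparison on sudden death and on all-cause death. Both are already named as outcomes in section 2.4. Make sudden death identifiable as its own component.
2. Report VT/VF separately for each group, as percentages and person-year rates, with no between-group hazard ratio.
3. In Table 4, define the VT/VF endpoint as sustained VT/VF or VT/VF with appropriate therapy. Record non-sustained runs and inappropriate shocks separately, and state that they are excluded.
4. Add unequal detection of arrhythmia to the limitations, next to confounding.

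The cost is a change of analysis wording and separate fields for the arrhythmia item, unless the full case report form already has them. The statistical price is fewer events and wider intervals in the between-group comparison.

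### The only VT definition stated (five or more beats) is the article's own NSVT threshold, leaving the VT/VF and sudden death comparison open to brief runs and unequal detection

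*Protocol article*

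**What the plan says.** Three tables in the protocol article bear on this point.

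- **Table 3 (follow-up events), item 1:** "Presence of VT (five or more consecutive beats), VF, and/or shock events (including inappropriate shocks"). VT, VF and every kind of shock share one item.
- **Table 2 (registration):** "Presence of NSVT (≥5 beats"). The same number of beats is here called non-sustained VT.
- **Table 4 (secondary endpoints):** "1. VT/VF and Sudden death". Its footnotes define sudden death and major bleeding, but not VT.

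Elsewhere the article separates brief from sustained VT. In section 2.2, primary-prevention patients qualify "irrespective of whether they've experienced NSVT", whereas the secondary-prevention criterion includes "sustained VT or unknown syncope, not due to reversible causes". No duration is attached to the sustained form.

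Section 2.6 gives VT/VF and sudden death particular attention among the clinical events. In primary prevention it is compared between the ICD/CRT-D group and the no device/CRT-P group by Kaplan–Meier and log-rank, and again by hazard ratio after propensity matching. The planning rate is introduced with "Considering the low incidence of VT/VF and sudden death in primary prevention (approximately 5%–10"%), and the sources cited just before it count other events. For one of them, "the annual occurrence rate of appropriate therapy for VT/VF with heart devices was approximately 6"%.

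**The concern.** A run that leaves a patient in the primary-prevention stratum at entry would, under the only follow-up rule stated, count as VT once enrolled. If that rule feeds endpoint 1, three things follow.

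1. Short runs may outnumber sustained VT, VF and sudden death, so the outcome would no longer describe the risk the study is about.
2. The observed rates could not be set beside the cited studies or the 5–10% figure. The stated reason for preferring propensity matching to multivariable Cox, namely few events, would rest on a different event.
3. The two groups do not have the same chance of a brief run being seen. From general knowledge of the devices rather than from the article, an ICD or CRT-D can record such runs continuously. For patients without a device, Tables 1 and 2 schedule an electrocardiogram at set visits and no ambulatory monitoring; Holter appears only at registration, as performed or not. Propensity matching balances measured baseline variables and does not correct unequal ascertainment.

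**Working it through.** **Planning figure.** No formula stands behind 5–10%, so it can only be checked against its sources in section 2.6: appropriate device therapy at about 6% a year; appropriate ICD operation above 6%; sudden cardiac death about 10% without and under 4% with an ICD. At 50:50 the last pair averages at most (10 + 4)/2 = 7%. These broadly fit 5–10%, but none counts five-beat runs. The mismatch is one of kind.

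**Events at the planning figure.** 651 × 0.05 = 33 and 651 × 0.10 = 65. At 10 events per covariate (assumption), that supports about 3 to 6 covariates. This is an upper bound, because the figure concerns the primary-prevention subset, whose size is not given.

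**When would brief runs dominate?** Let s be the proportion with a serious event, and b the proportion of the remaining patients who have only a brief run. The documents give no value for b, so a range is shown.

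- Total = s + (1 − s)b
- Brief-only share = (1 − s)b / total
- The share exceeds one half when b > s/(1 − s)

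Break-even b is 0.05/0.95 = 5.3%, 0.06/0.94 = 6.4% and 0.10/0.90 = 11.1% for s = 5%, 6% and 10%.

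With s = 6%:

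| b (assumed) | Total | Brief-only share | Events in 651 |
|---|---|---|---|
| 2% | 7.9% | 24% | 51 |
| 5% | 10.7% | 44% | 70 |
| 10% | 15.4% | 61% | 100 |
| 20% | 24.8% | 76% | 161 |
| 40% | 43.6% | 86% | 284 |

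At b = 2% the total stays inside 5–10%. From b = 10% upwards, 100 or more events would support 10 or more covariates, and the few-events argument weakens or fails.

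**Unequal detection.** Assume the same true serious rate of 6% in both groups, 325 patients per group (half of 651, again an upper bound), and brief runs detected in 20% of ICD and 5% of non-ICD patients without a serious event. All of these are illustrative.

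- ICD: 0.06 + 0.94 × 0.20 = 24.8%
- Non-ICD: 0.06 + 0.94 × 0.05 = 10.7%
- Apparent HR, non-ICD versus ICD: ln(1 − 0.107)/ln(1 − 0.248) = 0.40
- Events: 325 × (0.248 + 0.107) = 115. With that many events, the chance of p < 0.05 is above 99%, although the true serious rates are equal.

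**The case against.** The strongest reply is that Table 3 is a list of items to collect, not an endpoint rule. Its first item includes inappropriate shocks, which are not VT/VF, so it is wider than endpoint 1, and Table 4 does not import it. Detailed event definitions are commonly left to the full protocol or analysis plan. This stands in part: a reader might infer that the article fixes five beats as the endpoint threshold, and it does not say so. But it does state a VT definition, that definition collides with its own NSVT label, and the item as printed does not separate the components. That is more than omitted detail.

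A reader might also infer that the endpoint will consist mostly of short runs and that its rate will leave the 5–10% range. The documents do not support this, because they give no brief-run rate and low rates would leave the total within range. Part of any numerical gap would also be annual versus cumulative: 6% a year over a mean follow-up of about 1.88 years (midpoint of 1.00 and 2.75, assuming uniform accrual) is already 1 − exp(−0.06 × 1.88) = 10.6%.

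Further points stand. The 651 is a feasibility target, so no power calculation rests on 5–10%. More events would not invalidate propensity matching. This is a secondary endpoint in a registry whose primary endpoint is the device implementation rate, and the Discussion disclaims causal conclusions. Detection is also not all-or-none: the non-ICD group includes CRT-P, and Table 3 allows for loop recorders. None of this gives the section 2.6 comparison a VT definition that works alike in both groups.

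**Conclusion.** The concern holds in this form. The text alone establishes that five or more beats is the only VT definition stated, that Table 2 calls the same threshold NSVT, that Table 4 supplies no alternative, and that the planning rates count different events.

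The consequences are conditional on the Table 3 rule being used for endpoint 1. Domination by brief runs then needs a brief-run-only incidence above about 5–11%, depending on the serious-event rate. The apparent hazard ratio of 0.40 shows what unequal detection could do under assumed rates; it does not predict the result. Its direction would be to make the ICD/CRT-D group look worse on VT/VF. The primary endpoint is unaffected. The matter deserves correction because the affected comparison is one the article singles out and the remedy is cheap.

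**What to change.** Before between-group outcomes are examined, so that the definition is not chosen with results in view:

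1. Reconcile Tables 2, 3 and 4 on what VT means.
2. Split Table 3 item 1 into NSVT (five or more beats), sustained VT, VF, appropriate shocks and inappropriate shocks.
3. State for Table 4 item 1 a VT definition distinct from NSVT that can be ascertained in both groups. The threshold is for the investigators to set; referring only to sustained VT is not enough, since the article gives it no duration.
4. Report NSVT, device therapy and inappropriate shocks separately and descriptively. Appropriate device therapy should not be a component of the compared endpoint, because patients with no device or a CRT-P cannot receive defibrillator therapy.
5. Tie the 5–10% figure to the chosen definition, and say whether it is annual or cumulative.

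The cost is one revised field, re-coding of events already entered from source records, and fewer counted events. Some unequal detection of VT will remain and should be stated as a limitation.
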